# Shema

- Main eligibility criteria: Patients with an estimated glomerular filtration rate (eGFR) of less than 45 mL/min/1.73 m2 who attend the Mie Chuo Medical Center of the National Hospital Organization
- Timing of patient registration: The first day of the patient's visit to the pharmacy of the cooperating facility during the enrollment period
- Number of cases and registration period: 40 people, December 2022 ~ February 28, 2023
- Intervention Methods:

1. Questionnaire survey on awareness of the intake of potassium-containing foods

2. Dietary guidance: Nutritional guidance using explanatory documents on diet

3. Measurement of resting blood pressure after visit

4. Sharing information on the status of potassium adsorbents with Mie Chuo Medical Center

- Follow-up period: 3 months (after 84 days) from the first day of intervention

Study design

- positive
- Intervention Studies
- Design features: Before-and-after comparison test, open design
- Contrast Type: None
- Facility: Multi-center
- Randomization: No
- Level of Blinding: Open-label

[figure not shown]

## Summary of study design

Prospective intervention, before-and-after comparison, open design

This research will be conducted in compliance with the Personal Information Protection Law, the Declaration of Helsinki, and the Ethical Guidelines for Life Science and Medical Research Involving Human Subjects.

## Head of Data Management

Do not install.

## Person in charge of monitoring

Not applicable.

## Audit Officer

Not applicable.

# Purpose and Significance of Research

## purpose

In patients with chronic kidney disease (CKD), in addition to conventional medication guidance, nutritional guidance on potassium restriction for a few minutes by a pharmacy pharmacist will clarify the effect on serum potassium levels.

The primary endpoint is serum potassium level, and the secondary endpoint is resting blood pressure after visit, and change in the patient's awareness of potassium restriction.

### Primary Objective

(1) Changes in serum potassium levels before and after intervention

(2) Changes in awareness of the intake of potassium-containing foods before and after the intervention

### Secondary Objectives

| Secondary Objectives | Evaluation items | Reasons and Validity for Selection of Evaluation Items |
| --- | --- | --- |
| Change in Attitudes Toward the Intake of Potassium-Containing Foods | Survey Results | Evaluated on a 5-point scale for questions about awareness of potassium restriction |
| Change in resting blood pressure before and after intervention | Systolic and diastolic blood pressure at rest at visit | Blood pressure fluctuations are expected due to diet |

## background

As of 2016, approximately 330,000 patients with CKD with severely reduced renal function were reported, and further increases are expected in the future1). Patients with CKD have a variety of adverse events associated with decreased renal function, but hyperkalemia in particular is the most common electrolyte abnormality and can cause arrhythmias and sudden death.

Hyperkalemia is triggered by excessive dietary potassium intake2), so it is important for many patients with CKD to be guided to limit potassium intake. However, during inpatient treatment, the patient shows an appropriate serum potassium level due to strict control of diet and drug therapy, but after discharge from the hospital, it is not possible to maintain diet and adherence to potassium adsorbents, so there are some cases of emergency hospitalization for hyperkalemia.

## Significance of the study

Health insurance pharmacies that contribute to community-based medical care may be able to motivate patients to maintain a diet at home and prevent emergency hospitalization due to hyperkalemia by providing nutritional guidance for potassium restriction. Hyperkalemia may improve the patient's life prognosis due to fatal adverse events.

# Method and duration of the study

## Study design (research method)

・Case registration

CKD severity classification stages G3b, G4, G53^)^

When the outpatient prescription of the Mie Chuo Medical Center is brought to the insurance pharmacy, the written consent of the patient is obtained and registered. The date of obtaining consent shall be Day 1.

・Intervention method

All of the following interventions are performed by pharmacists at insurance pharmacies.

Date of Obtaining Consent (Day 1)

1. Questionnaire of the Awareness Survey on the Intake of Potassium-Containing Foods in Patients (Questionnaire 1) Appendix 2

2. Dietary guidance: Guidance on nutritional guidance for CKD (Annex 1) will be used. (Recommendation of nutritional guidance to the Nutrition Management Office as necessary)

3. Measurement of resting blood pressure after the visit

4. Provision of information to the Mie Chuo Medical Center on the status of the administration of potassium adsorbents: If the cause of poor adherence is the dosage form or dosage, the information will be provided to the Mie Chuo Medical Center of the prescriber in a tracing report.

⇒ hospital pharmacist writes details such as dosage status on the bulletin board of the electronic medical record to the prescribing physician and proposes a dosage change.

Day1-83

1. Dietary guidance (as appropriate)

2. Measurement of resting blood pressure after the visit

3. Confirmation of the status of potassium adsorbents (if information is provided to Mie Chuo Medical Center, confirmation of dosage type change, etc.)

After Day 84 (end date of the observation period)

1. Questionnaire on the Awareness Survey on the Intake of Potassium-Containing Foods by Patients (Questionnaire 2) Appendix 3

2. Measurement of resting blood pressure after the visit

3. Confirmation of the status of potassium adsorbents (if information is provided to Mie Chuo Medical Center, confirmation of dosage type change, etc.)

Contents of the questionnaire

For all questions, set a five-level answer.

At the time of obtaining consent (Day 1): Questionnaire 1

Q1. Do you know that potassium in the blood should not be too high?

Q2. Do you know of any foods that contain a high amount of potassium?

Q3. Are you conscious of refraining from foods that contain a lot of potassium?

Q4. Is it annoying (troublesome) to be aware of potassium intake?

3 months after obtaining consent (after Day 84): Questionnaire 2

Q1. Do you know that potassium in the blood should not be too high?

Q2. Do you know of any foods that contain a high amount of potassium?

Q3. Are you conscious of refraining from foods that contain a lot of potassium?

Q4. Is it annoying (troublesome) to be aware of potassium intake?

Q5. Has this guidance made you more careful about your intake of foods that contain potassium?

Q6. Do you want to continue to take measures against potassium-containing foods in the future?

Q7. Please let us know if there are any points that you have noticed through this guidance.

・Observation period

Calculated from the date of obtaining consent (Day 1) and after week 12 (Day 84)

・Data acquisition

During the observation period, each visit to the insurance pharmacy, the resting blood pressure (systolic blood pressure, diastolic blood pressure) is measured and recorded. The present study will be conducted in a non-randomized manner.

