## data collection

## Forms and Submission Deadlines

In this study, the results of the questionnaire before and after the intervention and the following items using Google Forms will be submitted to the principal investigator. The deadline for submission of the following items using Google Forms is within one week after the end of the patient's observation period.

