## How to send

For items in Google Forms, use the submission form on the Web. The results of the questionnaire will be sent by fax.

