# Procedures for obtaining informed consent, etc.

Explanatory documents and consent forms will be prepared by the principal investigator. It will be used after obtaining the approval of the Ethical Review Committee and the permission of the head of the research institution. If you want to revise it, apply to the Ethical Review Committee again, obtain approval, and use it after obtaining permission from the head of the research institution.

In this study, explanations and consent will be obtained by pharmacists at the counter of insurance pharmacies of joint research institutes. Specifically, the director of each joint research institute will explain the outline of the study and the data to be acquired using explanatory documents, and obtain consent from the patient himself/herself. Withdrawal of consent shall be made promptly upon request from the patient and with the signature of the consent withdrawal form.

As a general rule, the matters to be explained to the research subjects when receiving informed consent are as follows. However, this does not apply to matters approved by the head of the research institution in response to the opinion of the Ethical Review Committee.

(1) The name of the research and the fact that permission has been obtained from the head of the research institution to conduct the research.

(2) The name of the research cooperating organization pertaining to the research subject, the name of the person who only provides existing samples and information, the name of the organization to which he belongs, the name of all the principal investigators, and the name of the research institution

(3) Purpose and significance of research

(4) Methods of research (including the purpose of use and handling of samples and information obtained from research subjects) ) and period

(5) Reasons for selection as research subjects

(6) Burden on research subjects and anticipated risks and benefits

(7) The fact that the research can be withdrawn at any time even if the person agrees to the conduct or continuation of the research (if it may be difficult to take measures in accordance with the content of the withdrawal from the research subject, etc., that fact and the reason for the withdrawal will be included). ）

(8) The fact that the research subject will not be treated unfavorably by not agreeing to the conduct or continuation of the research or withdrawing the consent.

(9) Method of disclosure of information on research

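### Pharmacy pharmacists deliver both the guidance and the awareness questionnaires, with no private completion or sealed return, so part of any awareness gain could be courtesy

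*Protocol*

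**What the plan says.** Section 3.1 of the Protocol introduces its list of study steps with "All of the following interventions are performed by pharmacists at insurance pharmacies". On Day 1 the list contains "Questionnaire of the Awareness Survey on the Intake of Potassium-Containing Foods in Patients (Questionnaire 1) Appendix 2", followed by the dietary guidance. Guidance may be repeated up to Day 83. After Day 84 the list contains "Questionnaire on the Awareness Survey on the Intake of Potassium-Containing Foods by Patients (Questionnaire 2) Appendix 3". Under section 6, "explanations and consent will be obtained by pharmacists at the counter of insurance pharmacies of joint research institutes".

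Section 3.4 says that the questionnaire results "will be submitted to the principal investigator" and, under How to send, "The results of the questionnaire will be sent by fax". The sender is not named.

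Questionnaire 2 repeats items Q1 to Q4 and adds others, among them item Q5: "Has this guidance made you more careful about your intake of foods that contain potassium".

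The schema states "Level of Blinding: Open-label" and no comparison group. Awareness is rated by the patient on five levels (sections 2.1.2 and 3.1) and tested by Fisher's exact or chi-square test at a two-sided 5% level (section 3.5.2). Section 2.1.1 lists it as a primary objective; sections 2.1 and 2.1.2 treat it as secondary.

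**The concern.** Awareness is purely self-reported. The patient reports it through the pharmacy whose pharmacists obtained consent, gave the guidance and hand out the form, and no step keeps the answers from them. A general wish to look good may be present at both visits and would then largely cancel. A wish to credit the guidance can arise only once there has been guidance to credit, so it adds to the second measurement and does not cancel. Item Q3 asks whether the patient tries to avoid potassium-rich food, which is the behaviour that the pharmacist has been encouraging.

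At stake is the reading of the awareness result. In an open single-arm study no concurrent group would show the same drift, so analysis cannot split a gain into real change and courtesy. Awareness also defines subgroups in section 3.5.3, and section 2.1.1 gives it primary standing.

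**Working it through.** **What the text fixes and what it leaves open**

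| Point | Protocol |
| --- | --- |
| Who handles guidance and both questionnaires | Pharmacists at the insurance pharmacies (3.1) |
| Same individual for both tasks | Not stated |
| Self-completed or read out | Not stated; Appendices 2 and 3 are not in the text at hand |
| Return route | Fax, sender not named (3.4); the pharmacy is a natural inference |
| Private completion, sealed return, assurance to the patient | None stated |
| Baseline for the item | Q1 to Q4 yes; Q5 and Q6 no (3.1) |
| Comparison group | None (schema) |

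**Number of patients.** The Protocol has no sample size for awareness. Its 34 (target 40) is for serum potassium. It reproduces with a paired t-test, difference/SD = 0.5/1.0 = 0.5, two-sided 5% level and 80% power: power is 0.808 at n = 34 and 0.869 at n = 40. This requires reading the printed α and β as interchanged. I take n = 40 below.

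**Illustration under the named test.** Assumptions, none of them in the Protocol: each item is split into favourable or not; true awareness does not change; a share p1 is favourable on Day 1; a share q of the unfavourable patients answers favourably after Day 84 only to please; the two visits are treated as independent samples, as a Fisher test of before against after does.

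Favourable share at the second visit: p2 = p1 + (1 − p1)q. For example, p1 = 0.30 and q = 0.30 give 0.30 + 0.70 × 0.30 = 0.51.

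Chance of a significant result = the sum over i, j of Bin(i; 40, p1) × Bin(j; 40, p2), taken over the pairs (i, j) with two-sided Fisher p < 0.05.

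| q | p1 = 0.30: p2 | significant | p1 = 0.50: p2 | significant |
| --- | --- | --- | --- | --- |
| 0 | 0.30 | 2.8% | 0.50 | 3.3% |
| 0.1 | 0.37 | 6.4% | 0.55 | 5.1% |
| 0.2 | 0.44 | 18.7% | 0.60 | 10.8% |
| 0.3 | 0.51 | 40.4% | 0.65 | 21.3% |

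So q of 10 to 30% gives about 5 to 40%, against about 3% with no shift. The 3% lies under 5% because Fisher's test is conservative, and it counts both directions. At n = 34 the figures are slightly lower.

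**Does the choice of test matter?** Take instead a shift of 0.25 or 0.5 level with an SD of change of 1.0 level.

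- Paired t-test on the scores, noncentrality = (shift/SD) × √n. For example, 0.25 × √40 = 1.58 and 0.5 × √40 = 3.16. Chance of significance at n = 34 and n = 40: 29.3% and 33.8% (0.25 level); 80.8% and 86.9% (0.5 level).
- Fisher test on the dichotomised item, with latent normal answers of SD 1 at each visit and correlation 0.5, so that the SD of change is √(2 × (1 − 0.5)) = 1.0, and the cut at the median or 0.5 SD either side: about 4 to 6% (0.25 level) and 18 to 31% (0.5 level).

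The paired t figures do not describe the planned analysis. The Fisher figures do, under the stated assumptions.

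**The case against.** The strongest reply is that the mechanism is partly inferred. A reader might conclude that the very pharmacist who gave the guidance reads each answer and that the pharmacy sends the fax. The Protocol says neither: it names pharmacists as a group, is silent on how the form is completed and does not name the sender. That stands. What remains is that the text permits this arrangement and contains no safeguard against it.

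A reader might also say that the pressure exists only at the second visit. It does not: pharmacists have just obtained consent when Questionnaire 1 is answered, and item Q3 invites a favourable answer then too. Only the increment after guidance matters, and its size is unknown. Item Q5 has no baseline, so it cannot bias a before/after comparison; its weakness is that it stands alone.

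Figures of 29 to 34% or 81 to 87% are tempting, but they belong to a paired t-test that section 3.5.2 does not plan for the questionnaire. The table above also ignores pairing: if patients' answers were very stable between visits, the rates at these values of q would be lower.

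Finally, serum potassium comes from routine medical records (section 3.6.1) and is untouched, the study calls itself exploratory (section 20), and some expectation effect is inherent in an open single-arm study. All of this limits the consequence. It does not remove the case for a cheap safeguard at collection. Sealed forms will not stop patients knowing that the guidance is being evaluated, so the safeguard reduces the bias and does not abolish it.

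**Conclusion.** The point holds in a limited form. The Protocol assigns guidance and both awareness questionnaires to pharmacists at the same pharmacies, returns the results by fax and provides no privacy for the answers. Part of a gain on items Q1 to Q4 could therefore be courtesy that arises after about 12 weeks of guidance, and the design gives no means of separating it later.

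The size is not known. The range of about 5 to 40% against about 3% rests on an assumed 10 to 30% of initially unfavourable patients answering to please, a baseline favourable share of 30 or 50%, a dichotomised item, independent samples and n = 40. It shows that a moderate shift is enough to matter; it is not a forecast. The documents do not support the stronger inference that a positive awareness result would be courtesy alone. The primary serum potassium comparison is not affected.

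**What to change.** In sections 3.1 and 3.4, state that:

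- the patient completes both questionnaires alone, marked with the study number only;
- the patient is told that the pharmacist will not see the answers;
- the patient seals the form in an envelope, which the pharmacy collects at the visit and forwards unopened to the research secretariat, in place of the fax;
- if a patient needs help to read or write, the form is marked as assisted.

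State also that the awareness result is supportive of the serum potassium result, and bring section 2.1.1 into line with sections 2.1 and 2.1.2.

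The cost is about 80 envelopes (2 × 40) and a few lines of text; no visit, sample size or endpoint changes. The downside is some blank items, because completeness cannot be checked at the counter. Collecting the sealed form at the visit is preferable to posting by the patient: Per Protocol membership requires Questionnaire 2 (section 3.5.1), so a posted form that never arrives would remove the patient from that set for serum potassium as well.

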## Number of Planned Research Subjects and Rationale for Establishment

### Number of Planned Research Subjects

40 cases at the joint research facility

### Rationale for setting the number of planned research subjects

Previously, nutritional guidance on a potassium-restricted diet reduced serum potassium levels by up to 0.5 mmol/L4^).^ In general, it has been reported that the standard deviation of serum potassium levels between individuals was about 0.5 mmol/L5^).^ However, Kurita et al.5) report a standard deviation of n = 60-70, and the standard deviation in this study may be larger than previously reported. Therefore, the standard deviation in this study was estimated to be 1.0 mmol/L. Assuming that α = 0.8, β = 0.05, the standard deviation of the serum potassium level in the population is 1.0 mmol/L, and the difference in the mean value due to the intervention is 0.5 mmol/L in the paired t-test, the required number of cases is calculated as n=34. Taking into account the number of dropouts, the goal was n = 40.

During the three-month period from May 1 to July 31, 2022, 1,344 patients (eGFR <45 mL/min/1.73 m2 and serum potassium level of 4.0 mmol/L or higher) at Mie Chuo Medical Center were 1,344, and many of them visited the insurance pharmacy of the joint research institute.

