### Statistical analysis

(1) Primary endpoint

The mean and standard deviation of serum potassium levels before and after the intervention will be calculated, and a paired student's t-test will be performed at 5% on both sides of the significance level.

(2) Secondary endpoint

The mean and standard deviation of resting blood pressure before and after the intervention will be calculated, and a student's t-test will be performed with a significance level of 5% on both sides. For the content of the questionnaire, Fisher's exact test or chi-square test will be performed at a significance level of 5% on both sides of the change in awareness of potassium limitation.

(3) Comparison of patient backgrounds

Nutritional guidance will be used to compare the patient's background between the improved and non-improving serum potassium groups. For the nominal variables of gender, medical history, medication administration at home, and eating at home, Fisher's exact test or chi-square test is performed at 5% on both sides of the significance level. For the continuous variables age, Body mass index, and eGFR, the mean and standard deviation are calculated, and a student's t-test is performed with a correspondence of 5% on both sides of the significance level.

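### The sample-size paragraph prints α = 0.8 and β = 0.05 against a two-sided 5% test, and names the wrong SD for a paired t-test; n = 34 itself reproduces at α = 0.05 and 80% power

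*Protocol*

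**What the plan says.** Protocol section 3.2.2 (Rationale for setting the number of planned research subjects) builds the sample size in four steps.

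- It takes a reduction of up to 0.5 mmol/L from earlier work on potassium-restricted diets.
- It reports that "the standard deviation of serum potassium levels between individuals was about 0.5 mmol/L".
- It says that the cited cross-sectional study of CKD patients' adherence to treatment "report a standard deviation of n = 60-70, and the standard deviation in this study may be larger than previously reported", and concludes: "Therefore, the standard deviation in this study was estimated to be 1.0 mmol/L".
- It then calculates: "Assuming that α = 0.8, β = 0.05, the standard deviation of the serum potassium level in the population is 1.0 mmol/L", with a mean difference of 0.5 mmol/L in a paired t-test. The result is n = 34, raised to 40 for dropouts. No dropout rate is given.

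Protocol section 3.5.2 (Statistical analysis), item (1), sets the primary analysis as a paired Student's test: "t-test will be performed at 5% on both sides of the significance level".

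The protocol gives neither an SD for the within-patient change in potassium nor a before/after correlation.

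**The concern.** Three things in section 3.2.2 do not fit together.

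1. **Error rates.** Taken as printed, the type I error is 80% and the power 95%. The first contradicts the 5% two-sided level in section 3.5.2. If the 5% is taken from section 3.5.2 and β from section 3.2.2, the trial appears to have 95% power.
2. **Which SD.** A paired t-test works on the within-patient differences, so the SD that sets n is the SD of the change. The protocol enters "the standard deviation of the serum potassium level in the population is 1.0 mmol/L", an SD of levels derived from a between-individual figure.
3. **Why 1.0.** The only reason given for going from about 0.5 to 1.0 is the size of the sample in the cited study. A smaller sample estimates an SD less precisely. It does not make the population SD larger.

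At stake are the operating characteristics that the trial claims, and whether anyone can tell which assumption about variability n = 34 rests on.

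**Working it through.** **Inputs from the protocol:** mean difference δ = 0.5 mmol/L, SD 1.0 mmol/L, paired t-test, n = 34, target 40 (section 3.2.2); two-sided 5% level (section 3.5.2). **Assumed, not in the protocol:** any before/after correlation ρ.

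**Step 1: reproduce 34.** Enter 1.0 as the SD of the change, σ_d. The exact power of a two-sided paired t-test comes from the noncentral t distribution with n − 1 degrees of freedom and noncentrality (δ/σ_d)√n = 0.5√n.

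| Two-sided α | Power required | n needed |
|---|---|---|
| 0.05 | 0.80 | **34** (80.8% at 34; 79.5% at 33) |
| 0.8 (as printed) | 0.95 (as printed β) | 12 |
| 0.05 (section 3.5.2) | 0.95 (as printed β) | 54 |

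The normal approximation for the first row is (1.960 + 0.842)² × (1.0/0.5)² = 31.4, so 32; the t distribution brings it to 34. A one-sided 5% test at 80% power would need 27. Of these readings, only two-sided α = 0.05 with power 0.80 returns the protocol's figure. So 0.8 is the power and 0.05 is the α, and β should read 0.20.

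Under that reading, power is 80.8% at n = 34 and 86.9% at n = 40. The target of 40 is consistent with 15% dropout, since 34/0.85 = 40.

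**Step 2: SD of levels against SD of change.** With equal SDs σ before and after, σ_d = σ√(2(1 − ρ)). This equals σ only when 2(1 − ρ) = 1, that is ρ = 0.5. For δ = 0.5 and two-sided α = 0.05:

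| Assumed ρ | σ = 1.0: σ_d | n for 80% | power at 34 | σ = 0.5: σ_d | n for 80% | power at 34 |
|---|---|---|---|---|---|---|
| 0 | 1.414 | 65 | 51.7% | 0.707 | 18 | 97.9% |
| 0.3 | 1.183 | 46 | 66.7% | 0.592 | 14 | 99.8% |
| 0.5 | 1.000 | 34 | 80.8% | 0.500 | 10 | >99.9% |
| 0.7 | 0.775 | 21 | 95.5% | 0.387 | 7 | >99.9% |

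What 34 delivers therefore depends on whether 1.0 is an SD of levels or of change. The protocol's words say levels; its arithmetic treats it as change.

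**Step 3: is 1.0 defensible as an SD of change?** The largest value of σ√(2(1 − ρ)) is 2σ, reached at ρ = −1. At the cited σ of about 0.5 that is 2 × 0.5 = 1.0. So if the before and after SDs are both about 0.5, the SD of change cannot exceed about 1.0 at any correlation, and 34 patients give at least 80.8% power for a 0.5 mmol/L change. This is a valid argument for 1.0, and the protocol does not make it.

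**The case against.** The strongest reply is that this is a slip of labels. Section 3.5.2 fixes the significance level that will be used, n = 34 reproduces exactly once the labels are put right, and anyone who sees α = 0.8 will notice the error. The doubled SD errs on the safe side: in the paired formula n grows with the square of the SD, so going from 0.5 to 1.0 raises n from 10 to 34. The sentence about 60-70 also reads like a damaged translation, so the authors' reasoning may have been better than the text shows. Most of this stands, and it limits the point to a correction of wording. It does not remove the contradiction between the two sections, or the misdescription of the SD, from the only paragraph that justifies the sample size.

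Three stronger readings are tempting and are not supported.

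- **That 34 fails to deliver what is stated.** Read literally, α = 0.8 and β = 0.05 need 12 patients, and 34 would give 99.7% power. With the labels corrected, 34 is exact. It falls short (54 needed) only if α is taken from section 3.5.2 and β from section 3.2.2, a pair that the protocol states nowhere. Even that pair is met by 34 if 1.0 is an SD of levels and ρ is 0.7, but no correlation is stated.
- **That the trial is underpowered because the SD of change is larger than 1.0.** The figures of 65 patients and 52% power need a level SD of 1.0, twice the only cited value, together with zero correlation. Neither is established.
- **That 0.5 mmol/L is a best case, so true power is lower.** The protocol openly calls it an upper figure. How far smaller the effect might be rests on a cited source that is not at hand, and asking for power at smaller effects is a preference.

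**Conclusion.** The point holds as an error of statement. Section 3.2.2 prints error rates that contradict section 3.5.2 and cannot produce the stated n. The design that produces it is two-sided α = 0.05 with power 0.80, giving 80.8% power at 34 and 86.9% at 40, not the 95% that β = 0.05 implies. The section also describes as an SD of levels what the paired calculation uses as an SD of change, and gives an invalid reason for its size.

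The power figures assume a mean change of 0.5 mmol/L and an SD of change of 1.0 mmol/L. The statement that 1.0 is a safe upper value assumes that the cited between-individual SD of about 0.5 applies here both before and after the intervention. A reader might infer that 34 or 40 patients are too few; the protocol's figures do not show that.

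**What to change.** Rewrite the calculation in section 3.2.2 as follows.

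- Two-sided α = 0.05 and power 80% (β = 0.20), matching section 3.5.2.
- Mean change 0.5 mmol/L, and an assumed SD of the *within-patient change* of 1.0 mmol/L.
- Required n = 34, target 40, with the dropout allowance stated (the two figures imply 15%).
- Delete the argument from the cited study's sample of 60-70. A valid replacement is that, with before and after SDs of about 0.5 mmol/L, the SD of change cannot exceed about 1.0 at any correlation, so 1.0 is a conservative bound. No correlation then has to be assumed.

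The cost is one paragraph of protocol wording. The number of patients, the primary test and its level stay as they are. The stated power becomes 80% instead of an apparent 95%.
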